### Sample size {14}

All statistical methods and power analysis were developed through consultation with an independent statistician. Power analysis was performed with G*power 3.1 Software. To achieve a minimum 80% statistical power with an alpha value of 0.05, power analysis based on a hypothesised mean residual side-to-side difference of 2 mm of anteroposterior tibial translation yielded a sample size of *n*=48 (24 per group) utilising an expected independent *t*-test [47–50]. Although previously published KT-1000 data was utilised for power analysis, it has been shown that the GNRB exhibits similar absolute measures in side-to-side anterior tibial translation to KT-1000 utilised by experienced observers, whilst having reduced scatter around the mean [38]. This would mean that utilising KT-1000 published data to establish a power analysis would be a conservative method, and likely over-estimate the required sample size to detect significant differences.

Secondary power analysis based on 2-year IKDC total scores yielded a total sample size of 48 (*n*=24 in each group) to detect significant differences with 80% power and an alpha value of 0.05 with an anticipated independent sample two-tailed *t*-test. This is based on a previous retrospective study of suture-tape ACL reconstruction which reported a mean change from baseline IKDC of 56 ± 17 in SA-augmented ACLR, compared with 38 ± 25 in conventional ACLR [29, 51]. Secondly, previous studies evaluating the IKDC [51] which reported that a change score of 12.8 points would be sufficient to detect differences between those who have and have not had improved knee outcomes. Power analysis yielded a sample size of 48. Dropout rates are expected to be 30% based on institutional experience, owing to loss to follow-up and contralateral ACL rupture and graft failure, and as such 66 patients will be recruited. This is expected to take approximately 1–2 years of recruitment based on historical institutional caseloads.

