## Statistical methods

### Statistical methods for primary and secondary outcomes {20a}

Side-to-side difference in anterior tibial translation (the primary outcome), overall ACL-RSI, EQ5D-5L, Marx activity scales, IKDC and KOOS-QOL will be calculated as means, with measures of dispersion reported as standard deviation. Differences between groups will be reported as mean differences, with dispersion reported with confidence intervals. Data normality will be assessed with the Shapiro-Wilk test for continuous parametric assessment. Between-group comparisons, such as the primary outcome of mean difference in GNRB anteroposterior laxity at 2 years, will be assessed with independent samples *t*-tests. If data is found to be non-parametric in distribution, the Wilcoxon rank sum test will be utilised. Comparison of two dichotomous variables, such as return to sport rates and complication rates, will be performed with Fischer’s exact test. Repeated measures such as GNRB measures and mean PROMs will be assessed using mixed effects linear analysis. All tests are two-sided. A *p* value of <0.05 will be considered the cut-off for statistical significance.

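### The 12.8-point IKDC change score is set beside the 18-point difference as a ground for 48 patients, but on the printed SDs 48 patients give about 53% power for 12.8 points

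*Protocol article*

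**What the plan says.** Sample size {14} contains two power analyses. The first, for side-to-side laxity, gives 48 patients and is not at issue here. The second concerns the IKDC: "Secondary power analysis based on 2-year IKDC total scores yielded a total sample size of 48", split 24 and 24, "to detect significant differences with 80% power and an alpha value of 0.05 with an anticipated independent sample two-tailed" t-test.

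Two supports follow. The first is a retrospective study of suture-tape reconstruction with a "mean change from baseline IKDC of 56 ± 17 in SA-augmented ACLR, compared with 38 ± 25 in conventional ACLR". The second, introduced as such, is that earlier work on the IKDC found that "a change score of 12.8 points would be sufficient to detect differences between those who have and have not had improved knee outcomes". The next sentence is "Power analysis yielded a sample size of 48", and the text then moves to dropout and the recruitment target of 66.

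No other IKDC standard deviation appears in the protocol. Statistical methods {20a} confirms the sidedness ("All tests are two-sided") and plans to report between-group mean differences with confidence intervals.

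**The concern.** As the paragraph is laid out, 12.8 points is listed among the grounds for the IKDC sample size and the 48 is restated immediately afterwards. The natural reading is that 48 patients give 80% power for 18 points and for 12.8 points alike. Both cannot hold at one SD: 12.8 is only 71% of 18 (12.8/18 = 0.71), and the required sample size grows roughly with the inverse square of the difference.

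There is also a mismatch of kind. The 12.8 figure is described as a change score that tells improved patients from non-improved ones. That classifies an individual. A two-sample t-test is powered on a difference between arm means, so such a threshold does not enter the calculation unless the plan says it is being used as a between-arm target.

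What is at stake is how the IKDC result is read. IKDC is the only patient-reported outcome with a power statement, and better patient-reported outcomes are a stated hypothesis (Abstract; Discussion). A reader who takes 80% power, 12.8 points and 48 patients as belonging together could treat a non-significant IKDC result as evidence against a 12.8-point difference.

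**Working it through.** **Inputs, all from the protocol.** Two-sided alpha 0.05; 80% power; 24 per group; 1:1 allocation; change-score means 56 and 38; SDs 17 and 25; change score 12.8.

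**Method.** Two-sample t-test, power from the noncentral t distribution with df = 2n − 2 = 46, d = difference/SD, noncentrality = d × √(n/2) = d × √12 = d × 3.464, critical t = 2.013.

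**Step 1: reproduce the plan's figure.**
- Pooled SD = √((17² + 25²)/2) = √457 = 21.38.
- Difference = 56 − 38 = 18; d = 18/21.38 = 0.842; noncentrality = 2.92.
- Power at 24 per arm = 81.5%, and 24 is the smallest group size that reaches 80%. Total = 48. The stated number reproduces.

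**Step 2: put 12.8 points in place of 18.**

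| SD used | d = 12.8/SD | Power at 24 per arm | n per arm for 80% | Total |
|---|---|---|---|---|
| 21.38 (pooled) | 0.599 | 52.8% | 45 | 90 |
| 17 (smaller) | 0.753 | 72.4% | 29 | 58 |
| 25 (larger) | 0.512 | 41.2% | 61 | 122 |

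At the pooled SD, a Welch version gives 52.6% and the normal approximation 54.5%, so the choice of method hardly matters. The totals are before any allowance for dropout.

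**Step 3: what would make 12.8 points give 48?** The standardised difference detectable with 80% power at 24 per arm is d = 0.826. The SD would then have to be 12.8/0.826 = about 15.5, below both printed SDs.

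**Step 4: what 24 per arm can detect.** At SD 21.38 the detectable difference is 0.826 × 21.38 = 17.7 points, which is 38% larger than 12.8 (17.7/12.8 = 1.38).

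**Step 5: no loss to follow-up.** If all 66 patients were analysed (33 per arm), power for 12.8 points at the pooled SD would be 66.8%.

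**Step 6: consequence for the interval.** The 95% confidence half-width at 24 per arm is 2.013 × 21.38 × √(2/24) = 12.4 points. A non-significant result with an observed benefit between about 0.4 points (12.8 − 12.4) and 12.4 points would therefore still have 12.8 inside its interval.

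**The case against.** The strongest reply is that the protocol makes no false calculation. The 48 is tied to the 56-against-38 comparison and is correct for it. The 12.8 sentence is a fragment without a main verb and gives no SD, power or sample size. It may have been meant only to show that the powered 18-point difference exceeds a threshold of clinical relevance, and the repeated 48 could simply restate the number common to the laxity and IKDC analyses before the dropout allowance. Part of this stands. A reader might infer that the stated 48 is wrong, or that the protocol asserts outright that 12.8 points yields 48. The document supports neither: the 48 reproduces, and no sentence makes that assertion. What remains is that the figure is introduced as a second ground and followed at once by the sample size, so the text invites a conclusion that its own numbers do not bear. If 12.8 was meant only as a relevance threshold, the paragraph still needs to say so.

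A second reply concerns the SDs. They are for change from baseline, while the power analysis is said to be for 2-year total scores. The Background describes the retrospective comparative study's change scores as 1-year results. A reader might infer that the shortfall holds for any IKDC score at any time point. That does not follow: the protocol prints no SD for 2-year totals, and one of about 15.5 would give 48. The calculation covers the printed SDs only.

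Third, confidence intervals are already planned, mixed models are planned for repeated measures, and IKDC is secondary. All true. The 53% is for a single unadjusted t-test with 48 completers. These points limit the consequence, but they do not make 12.8 points a support for 48.

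**Conclusion.** The point holds as a fault in the stated justification. On the only IKDC SDs in the document, 48 patients give 81.5% power for 18 points and about 53% for 12.8 points (41% to 72% across SDs of 25 to 17). The trial would miss a true 12.8-point between-arm difference about 47% of the time at the pooled SD. For 80% power it would need about 90 analysed patients (58 to 122). The conclusion assumes a two-sided t-test at 0.05, 24 completers per arm and the change-from-baseline SDs as printed.

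A reader might go further and infer that the trial is too small. The documents do not support that on this ground: IKDC is a secondary outcome, the laxity analysis has its own justification for 48, and nothing here touches it. Nor does the protocol call a 12.8-point difference between arms its target or the smallest that matters. The correction is worth making because it changes how a null IKDC result may be read, and it costs almost nothing.

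**What to change.** Revise the IKDC paragraph of Sample size {14} as follows:

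- Attribute the 48 to the 18-point difference in change from baseline only.
- State that with 24 per arm and an SD of 21.4 the difference detectable with 80% power is about 18 points, and that power for a 12.8-point between-arm difference is about 53%.
- Describe 12.8 as a within-patient threshold separating improved from non-improved patients, not as a basis for the sample size.
- Add that a non-significant IKDC result does not by itself exclude a 12.8-point difference, and that the result will be read from the confidence interval already planned in Statistical methods {20a}.

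If the investigators did use another SD with 12.8 points, they should print it with its source, score and time point, so that the 48 can be checked.

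The cost is a few sentences and a less favourable statement of IKDC power. Enrolment, the primary-outcome sample size and the planned analyses do not change.

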## Methods: participants, interventions and outcomes

### Study setting {9}

This study will be conducted across three subsidiary hospitals, within a single major metropolitan Australian academic hospital (site details available on ANZ Trial Registry). All patients will be recruited from the adult orthopaedic outpatient clinic. A total of 66 participants will be recruited and randomised to a treatment arm. Owing to the nature of the randomisation model, greater than 66 patients may be recruited to reach the eventual target randomisation number. All data will be collected within Australia.

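### Randomising 66 allows for about 27% dropout, not the 30% the protocol states; at 30% about 46 patients are evaluable instead of the 48 planned

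*Protocol article*

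**What the plan says.** Sample size {14} opens with the target: "To achieve a minimum 80% statistical power with an alpha value of 0.05". The primary calculation rests on a "hypothesised mean residual side-to-side difference of 2 mm of anteroposterior tibial translation" and arrives at 48 patients, 24 per group, with an independent t-test. A second calculation, on IKDC, also arrives at 48.

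The section then allows for losses: "Dropout rates are expected to be 30% based on institutional experience". It attributes them to patients lost to follow-up, graft failure and rupture of the opposite ACL, and concludes "and as such 66 patients will be recruited".

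Study setting {9} fixes what the 66 counts: "A total of 66 participants will be recruited and randomised to a treatment arm". It adds that more than 66 may be recruited, but only so that 66 are reached at randomisation. Statistical methods {20a} supplies the test conditions: "All tests are two-sided", and "A *p* value of <0.05 will be considered the cut-off for statistical significance".

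**The concern.** The wording presents 66 as the result of applying a 30% loss to 48 evaluable patients. Dividing 48 by the expected retention does not give 66, and neither does the common shortcut of adding 30% to 48.

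All the losses named occur after randomisation, and randomisation takes place during surgery once eligibility has been confirmed at arthroscopy. The permission to recruit more than 66 covers patients excluded before that moment, so it adds nothing for later losses. Under Plans to promote participant retention {18b}, no further data are collected after withdrawal or graft failure. Such patients would therefore have no 24-month arthrometer reading.

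At stake is whether the stated power target holds at the protocol's own dropout rate. A reader can check this figure with one division, and the recruitment target depends on it.

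**Working it through.** **Inputs**

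- Evaluable number required: 48, or 24 per arm (Sample size {14}).
- Dropout: 30% (Sample size {14}).
- Number randomised: 66 (Sample size {14}, Study setting {9}), allocated 1:1 (Sequence generation {16a}).
- Two-sided t-test at 0.05 (Statistical methods {20a}).
- IKDC change from baseline: 56 with SD 17 against 38 with SD 25 (Sample size {14}).
- Primary difference: 2 mm. The article gives no SD, so it is back-solved below as an assumption.

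**Step 1: try to reproduce 66**

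- Required N = 48 / (1 − 0.30) = 68.6, so 69. Per arm, 24 / 0.70 = 34.3, so 35, which makes 70.
- Shortcut: 48 × 1.30 = 62.4, so 63. Rounded up per arm, 24 × 1.30 = 31.2, so 32, which makes 64.
- None of these gives 66.

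**Step 2: what 66 does deliver**

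- Evaluable at 30% loss: 66 × 0.70 = 46.2, about 23 per arm.
- Loss that leaves 48: 1 − 48/66 = 27.3%.
- Shortfall in randomised patients: 69 − 66 = 3, or 70 − 66 = 4 for equal arms.

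**Step 3: power for IKDC**

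Power comes from the noncentral t distribution with 2n − 2 degrees of freedom and noncentrality d × √(n/2), where n is the number per arm.

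- Pooled SD = √((17² + 25²)/2) = √457 = 21.4, and d = (56 − 38)/21.4 = 0.842.
- n = 24: power 81.5%.
- n = 23: power 79.7%.

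This reproduces the protocol's 48, since 24 is the smallest n per arm that reaches 80%. It also shows that losing one patient per arm takes power just below 80%.

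**Step 4: power for the primary outcome**

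Assume that 24 per arm is the smallest n giving at least 80%. The SD then lies between two limits:

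| Condition | d | Implied SD = 2/d | Power at n = 24 | Power at n = 23 |
|---|---|---|---|---|
| n = 24 gives exactly 80% | 0.826 | 2.42 mm | 80.0% | 78.2% |
| n = 23 would only just reach 80% | 0.845 | 2.37 mm | 81.7% | 80.0% |

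Power at 23 per arm therefore runs from 78.2% to just under 80%, and the largest drop is 80.0 − 78.2 = 1.8 points. An uneven loss leaving 22 and 24 makes almost no difference: 78.2% at the first limit and 79.9% at the second.

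**The case against.** The strongest reply is that the mismatch has little consequence. It amounts to two evaluable patients, and 27% against 30% is within the uncertainty of a round figure drawn from institutional experience. The IKDC result at 23 per arm is 80% to the nearest whole percent. That stands, and it limits the weight of the point.

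A reader might infer that the trial misses 80% power for its primary outcome. The document does not establish this. The SD behind the 2 mm is not in the article, and 78.2% is only the lower end of what the text allows. The section also says: "Although previously published KT-1000 data was utilised for power analysis". It then argues that the GNRB gives similar averages with less spread, so the calculation should err on the large side. If so, 46 evaluable patients could give 80% or more. An SD of 2.2 mm, taken only as an illustration, gives 85.4% at 23 per arm. However, the protocol puts no figure on the reduction in spread. It offers the argument in support of the 48, not as a basis for the 66, and the argument does not bear on IKDC.

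Two other defences are weaker. The planned imputation under {20c} does not turn unobserved 24-month readings into observed ones, and the sample size section itself treats dropouts as lost from the 48. It might also be said that adjusting the primary analysis for baseline would recover the power. The planned test is an independent t-test, and no correlation between baseline and 24 months is given, so the document offers no support for that.

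**Conclusion.** Wrong as written, with a small effect. The inconsistency between 48, 30% and 66 is plain arithmetic and needs no assumption beyond reading 66 as the number randomised, which the protocol states.

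The effect on power is less certain. The IKDC figure rests on stated inputs only. The primary range rests on 24 per arm being the smallest sufficient size, on a back-solved SD of 2.37 to 2.42 mm, and on losses falling about equally on both arms. This is a misstatement in the sample size section and not evidence of a seriously underpowered trial.

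**What to change.** Restate the last part of Sample size {14} along these lines:

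> Randomising 66 patients allows for about 27% dropout from the 48 evaluable patients required. At 30% dropout, about 46 would be evaluable (23 per arm), and power would be slightly below 80% under the planning assumptions.

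The cost is one or two sentences and a slightly less favourable power statement. The planned analysis and the recruitment target stay as they are. If the sponsor prefers to keep the 30% allowance in full, the matching target is 70 randomised (35 per arm; 70 × 0.70 = 49 evaluable), four more patients. The size of the effect does not require that.

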### Recruitment {15}

Recruitment will be conducted continuously across patients eligible until the target randomised sample size is achieved. Based on institutional caseloads, it is anticipated this will take 1–2 years. A dedicated member of the research team will be tasked with recruitment on clinic days, such that all prospective participants are given appropriate opportunity to understand the study before and during involvement.

## Assignment of interventions: allocation

### Sequence generation {16a}

The randomisation design is a computer-generated permuted single-blind block randomisation. The randomisation sequence will be developed by an independent statistician, with all other research team members blinded to the randomisation sequence. Participants will be randomised using permuted block randomisation which allows for a better guarantee of equal-sized treatment groups [52] whilst protecting against prediction of allocation towards the end of the recruitment period. Randomisation will be allocated in a 1:1 fashion, whereby patients will undergo either standard ACLR or suture tape-augmented ACLR. Randomisation will be stratified according to age greater than 25 years.

### Concealment mechanism {16b}

The centrally managed, blinded randomisation model will ensure allocation concealment and prevent selection bias. The allocation sequence will be stored within the REDCap database and inaccessible to all but the statistician, ensuring concealment. Following randomisation, the allocation details will be displayed on the web-based system for each participant, and an automated email will be sent to members of the research team to ensure appropriate documentation in the medical record.

### Implementation {16c}

The allocation sequence will be developed by an independent statistician. It will be integrated into the REDCap automated randomisation platform and will be blinded to all other investigators. Enrolment of participants will be overseen by the lead surgeons, and associate investigators ST and LB, and will be carried out by associate investigators LH and EN. Randomisation and assignment to the intervention arm will be performed intraoperatively, following assessment and management of concomitant cartilage and meniscal injuries by the associate investigators LB and ST.

## Assignment of interventions: blinding

### Who will be blinded {17a}

Trial participants will be blinded to the allocation arm for the duration of the study. GNRB arthrometric measurements are inherently low in bias, secondary to the computer-generated application of force to the posterior tibia; however, technicians taking the measures will be blinded to allocation arm. Owing to the nature of examination assessments, the best technician to carry these out is the same as the treating surgeon and thus blinding is not appropriate in this setting. The questionnaire-based outcomes are patient-reported and therefore also assessor-blinded.

### Procedure for unblinding if needed {17b}

As the surgeon and only outcome assessors are not blinded, unblinding will not be required.

## Data collection and management

### Plans for assessment and collection of outcomes {18a}

All data will be entered into a custom web-based REDCap database accessible by study research staff only. All GNRB data will be transposed from automated Genuroub software outputs to custom-designed data entry forms in the preoperative and postoperative setting by a member of the research team specifically trained in both software. PROMs and return to sport data will be collected by a single questionnaire and entered directly via online surveys by the participant. All validated PROM scores are cited above and can be found in the original citation; all non-validated questionnaires are included in the Additional file 1 of this document. Examination findings will be entered specifically into the medical record of each participant, and a study-specific data collection form and transposed into the web-based database.

### Plans to promote participant retention and complete follow-up {18b}

PROMs and return to sport data will be collected by online survey, deliverable by email or text message with the aims to increase follow-up rates among a technologically inclined patient cohort. All follow-up examinations and GNRB assessments will be performed concurrently with follow-up surgical appointments until the 12-month mark in order to reduce the study burden on the individual. If a participant withdraws from the study, or suffers graft failure, no further data will be collected; however, data collected up until this point will be included in the study and absent data will be analyzed according to intention to treat principles.

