#### Criteria for discontinuing or modifying allocated interventions {11b}

Owing to the nature of the intervention, being a surgical technique and use of specific implant, and the timing following randomisation, it is not anticipated that any participants will be discontinued from allocated intervention following randomisation. If a participant suffers graft failure or contralateral ACL knee rupture, then analysis via GNRB assessment may be changed. Participants may withdraw from the study without citing a reason, but reasons may include the participant has chosen to withdraw, postoperative graft rupture or failure or the participant has experienced an adverse event. If a patient indicates that they wish to withdraw, this will be recorded in the REDCap project, and they will not be asked to complete any further research-only assessments. They will be reassured that they will continue to receive care and any subsequent management at Western Health. If a patient withdraws from the study, data collected to this point will remain within the study for analysis unless the participant specifically requests otherwise.

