### Outcomes {12}

#### Primary outcome

The primary outcome will be the side-to-side difference in anterior tibial translation as measured on the GNRB arthrometer at 2 years post-operatively, between groups. Maximum anteroposterior tibial translation at 134 N will be recorded on both the operative and non-operative knees pre-operatively and post-operatively at 3, 12 and 24 months. The goals of ACL reconstruction are to restore sagittal and rotatory stability to the knee and to prevent secondary injuries such as meniscal tears, and progression to osteoarthritis [35]. Common means of assessing this is by comparison of pre- and post-operative subjective Lachman manoeuvre and anterior drawer; however, these are often imprecise and subjective [36]. Consequently, devices to accurately measure anterior tibial translation have been developed, most popularly the KT-1000 ™ manual arthrometer (MEDmetric®, San Diego, USA) [37]. However, this device has been criticised for poor inter- and intra-observer reliability, and as such, newer computerised models such as the GNRB (Genourob, Laval, France) have been developed, with improved reliability [38]. Studies have utilised these arthrometers to compare between anterior cruciate ligament surgical techniques, such as graft types [39, 40], assessing post-operative outcomes [41], as well as analysing residual joint laxity after ligament reconstruction [42]. This outcome has been selected due to its ability to assess whether the addition of suture tape in ACLR results in knee stability that is more similar to the contralateral uninjured knee than standard ACLR technique. Anterior tibial translation and knee laxity may vary from individual to individual, and for this reason, side-to-side difference has been chosen as the primary outcome, allowing the contralateral knee to be a within-participant baseline measure, reducing the variability in outcome owing to between participant differences.

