### Methods in analysis to handle protocol non-adherence and any statistical methods to handle missing data {20c}

All principal analyses will be based on the intention-to-treat principle, analysing participants in the groups to which they are randomised. Missing data will be quantified and if possible multiple imputation will be used; otherwise, simple imputation will be used. Owing to the nature of enrolment and randomisation in this study, it is unlikely that a participant will be randomised and subsequently not receive the intervention, and thus adherence does not apply directly to the intervention arm.

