### Adverse event reporting and harms {22}

Participant safety will be ensured via standard institutional protocols. The use of the GNRB is established to be safe in pre-operative [53] and early post-operative patients [42], with no adverse events reported, and this will be expressed verbally to patients prior to participation. Adverse events are defined as medical occurrences that may or may not have a causal relationship with the surgical treatment administered. Any adverse events identified will be recorded and reviewed regularly by the Internal Trial Monitoring Committee. The Principal Investigator will determine causality. The number and type of adverse events (AEs) will be recorded up to 24 months. Any AEs will be noted on the REDCap database. These events will also be reviewed by the participants’ medical and surgical teams (who are not a part of the investigative team) as part of standard care.

Serious adverse events (SAE) are defined as any untoward and unexpected medical occurrence that results in death, is life-threatening, requires hospitalisation or prolongation of existing inpatients’ hospitalisation, results in persistent or significant disability or incapacity, is a congenital anomaly or birth defect, or is any other important medical condition which, although not included in the above, may require medical or surgical intervention to prevent one of the outcomes listed. All SAEs will be reported to the approving ethics board within 72 h of the investigators becoming aware of them. SAEs that may be expected as part of the surgical interventions and that do not need to be reported to the HREC are complications of anaesthesia or surgery (wound infection, bleeding or damage to adjacent structures such as nerves, tendons and blood vessels, delayed wound healing, and thromboembolic events, femoral or tibial fracture).

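### Follow-up stops at graft failure and the missing 24-month laxity has no handling rule of its own, so the primary difference can be biased in a direction set by which arm fails more

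*Protocol article*

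**What the plan says.** The primary endpoint is fixed at two years: "The primary outcome will be the side-to-side difference in anterior tibial translation as measured on the GNRB arthrometer at 2 years post-operatively, between groups".

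Five places bear on what happens to a participant whose graft fails before then:

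- **Retention {18b}:** "If a participant withdraws from the study, or suffers graft failure, no further data will be collected". Data already collected are kept, and "absent data will be analyzed according to intention to treat principles".
- **Discontinuing or modifying interventions {11b}:** graft rupture or failure is listed among possible reasons for withdrawal, and withdrawn participants are not asked for further research-only assessments. The section adds: "If a participant suffers graft failure or contralateral ACL knee rupture, then analysis via GNRB assessment may be changed". It does not say how.
- **Sample size {14}:** the expected 30% dropout arises "owing to loss to follow-up and contralateral ACL rupture and graft failure".
- **Missing data {20c}:** "Missing data will be quantified and if possible multiple imputation will be used; otherwise, simple imputation will be used". The analysis principle is: "All principal analyses will be based on the intention-to-treat principle, analysing participants in the groups to which they are randomised".
- **Adverse events {22}:** "The number and type of adverse events (AEs) will be recorded up to 24 months". The secondary outcomes section also plans a review of every patient's medical record at two years for complications, including graft failure.

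The Discussion explains that tape is meant to shield the graft while it matures and to protect grafts at higher risk of failing. It links early laxity to later graft failure. It also concedes that a trial of this size cannot feasibly investigate graft failure.

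**The concern.** Graft failure is a result of the operation, and it lies on the pathway the tape is meant to influence. The plan nevertheless gives it the same follow-up consequence as a participant leaving the study. The 24-month laxity is then missing because of something closely tied to laxity itself. A standard imputation, which assumes that missing values resemble observed ones given earlier data, is not credible for these knees.

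Two things are at stake. First, the primary difference may leave out the laxity contributed by failed grafts, and the error does not cancel when the arms fail at different rates. Second, 24-month patient-reported and return-to-sport outcomes are lost for the participants likely to have done worst. The imputation can be settled in an analysis plan. The loss of data cannot, because no analysis plan recovers measurements that were never taken.

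**Working it through.** **1. Following one failed graft through the protocol.** Suppose a graft fails at 15 months. Under {18b} collection stops. The two-year arthrometer visit is, per the participant timeline, the one attendance outside routine care, so the primary value is not obtained. Under {14} the participant is part of the dropout allowance. Under {20c} the value is imputed, with no distinction between failure and ordinary loss. Under {11b} the analysis might instead be altered in some unstated way. Meanwhile {22} and the two-year record review expect information on this participant up to 24 months. These statements cannot all be followed as written.

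**2. Size of the shift.** The protocol states no figure for this, so there is none to reproduce. Let p_S and p_T be the proportions failing before 24 months (standard, tape), E the mean excess laxity of a failed knee over what it would have shown intact, and D the standard-minus-tape difference had no graft failed.

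- Failures measured: D + (p_S − p_T) × E
- Failures imputed as if intact: D
- Shift: (p_S − p_T) × E

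Assumed inputs, none from the protocol: p_S 5–15%, p_T 2–5%, E 3–5 mm.

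| p_S | p_T | E (mm) | Shift (mm) | Share of 2 mm |
|---|---|---|---|---|
| 0.05 | 0.05 | 3 | 0 | 0% |
| 0.05 | 0.02 | 3 | 0.09 | 4.5% |
| 0.10 | 0.05 | 5 | 0.25 | 12.5% |
| 0.15 | 0.05 | 5 | 0.50 | 25% |
| 0.15 | 0.02 | 5 | 0.65 | 32.5% |

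Exchanging the arms' rates reverses the sign.

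**3. Check by simulation.** Settings: 33 per arm; correlation 0.6 between 12 and 24 months; failures after 12 months; failed knees imputed by regression on the 12-month value, fitted to intact knees in the same arm. The SD is not stated. The planned 24 per group at 80% power and two-sided 0.05 implies a standardised effect of 0.826, hence 2 / 0.826 = 2.42 mm.

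| Failure, standard vs tape | D (mm) | E (mm) | Measured (mm) | Imputed (mm) |
|---|---|---|---|---|
| 10% vs 5% | 2 | 3 | 2.14 | 2.00 |
| 10% vs 5% | 2 | 5 | 2.25 | 2.01 |
| 15% vs 5% | 2 | 5 | 2.48 | 1.98 |
| 5% vs 10% | 2 | 5 | 1.74 | 2.00 |
| 10% vs 5% | 0 | 5 | 0.25 | 0.01 |

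The imputed results sit at D throughout, as the formula predicts. Pre-failure readings do not recover the laxity that the failure itself causes.

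**4. Equal rates are not always harmless.** The formula takes E as equal in both arms. If failed knees instead reach the same absolute laxity in both arms, the arm with the tighter intact knees has the larger excess. With intact means of 3 and 1 mm, failed knees at 5 mm and 5% failure in each arm, the measured difference is 0.95 × (3 − 1) = 1.90 mm, against 2.00 mm if imputed as intact.

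**5. Scale.** The assumed rates mean 33 × 0.05 to 33 × 0.15, about 2 to 5 failures with standard surgery, and 33 × 0.02 to 33 × 0.05, about 1 to 2 with tape. At SD 2.42 mm the standard error of the difference is 2.42 × √(2/33) = 0.60 mm with 33 per arm and 2.42 × √(2/24) = 0.70 mm with 24.

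**The case against.** The case on the other side has real force on several points.

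- **A reader might infer that harm from tape would be hidden.** The documents do not support this. Graft failure is a named secondary outcome, captured by record review at two years, with complication rates compared by Fisher's exact test. What stands is that the Discussion itself says the trial is too small to investigate failure, so that comparison is a weak substitute for including failures in the primary result.
- **A reader might infer that the analysis is not intention-to-treat.** The missing-data section explains its principle as analysis by randomised group, and imputing within the assigned arm satisfies that. The open question is which treatment effect is estimated once a graft has failed.
- **A reader might infer that failed knees will certainly be imputed from intact ones.** No section says so. A failure indicator or a worst-case analysis could be in an analysis plan that is not shown. The bias is therefore conditional on an imputation that ignores failure. The stop on data collection is not conditional.
- **A reader might infer that collection also stops after contralateral rupture.** The retention section stops it only for withdrawal or graft failure. Contralateral rupture appears in the dropout allowance and in the open-ended sentence on arthrometer analysis, which fits loss of the reference knee.
- **The shift is small against sampling error.** Most of the illustrated range lies below one standard error, and if tape prevents failures the bias works against a superiority claim. Both are fair. Neither helps if tape fails more often, because the bias then favours tape.
- **Estimating laxity as if no graft had failed is a defensible target.** It is, if declared in advance. The protocol does not declare it.

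**Conclusion.** The point holds in a limited form. The protocol ends data collection at graft failure as if it were withdrawal, counts failure as dropout, sends the missing primary value to imputation without a separate rule, and keeps an undefined change of analysis available. The stop conflicts with the two-year record review and with adverse event recording to 24 months. It also loses 24-month patient-reported and return-to-sport data that cannot be reconstructed later.

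If the imputation does not account for failure, the primary difference shifts by 0 to 0.65 mm in the illustrated range, up to about a third of the 2 mm planning effect. The sign follows the arm with more failures. This rests on assumed failure rates, on assumed excess laxity equal in both arms, and on failed knees being imputed as intact. It should not be read as an estimate of the bias in this trial.

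**What to change.** 1. **Retention {18b}:** state that graft failure is not withdrawal. Unless consent is withdrawn, continue patient-reported, return-to-sport, adverse event and, where feasible, arthrometer collection to 24 months.
2. **Reconcile** {18b}, {11b}, {22} and the two-year record review in the secondary outcomes section, so that they give one rule on follow-up after failure.
3. **Discontinuing interventions {11b}:** replace the open-ended sentence with a pre-specified handling of graft failure in the primary analysis, including the treatment effect it targets. Do not impute failed knees as if intact.
4. **Sensitivity analysis:** rank failures worst, or use an arthrometer reading taken before any revision where one exists. A carried-forward reading is an assumption of its own, so it belongs here and not in the primary analysis.
5. **Contralateral rupture:** pre-specify in {11b} how the side-to-side difference is handled, for example a sensitivity analysis using the last pre-rupture reading of the non-operative knee. This mixes test occasions, so it should also stay a sensitivity analysis.

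The cost is protocol wording and a few more follow-up contacts. The surveys are already online, and the arthrometer is already used on ACL-deficient knees before surgery. The small downside is that any pre-revision value is measured earlier than 24 months.
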